## Abstract

Recent studies have established yoga practice as a mainstream complementary clinical tool within correctional environments. It is shown that regular yoga practice is coupled with improved impulse control, sustained attention, attenuated antisocial and self-harm behaviors, reduced stress, and psychological distress. No academic research until now has provided evidence of mental health benefits of yoga for institutionalized young people. In Sweden, each year more than thousand adolescents receive compulsory care at juvenile institutions run by the Swedish National Board of Institutional Care. These young people are characterized by substance abuse, aggressive and antisocial behaviors, high frequency of self-harm, and the experience of abuse. Most of them manifest attention problems, depression, anxiety, and impulsivity. They have a dramatically increased risk for recidivistic criminal behavior, continuous medical, and social care and untimely death. The present study plan aims at evaluating, with previously validated psychological measures, in a quasi-experimental design, the effects of yoga practice for institutionalized adolescents. Adolescents' experiences of participating in yoga practice will also be assessed by semi-structured individual interviews. Ethical approval was given by the Swedish Ethical Review Authority. It is hypothesized that yoga practice (in combination with the standard treatment within institutional care) will reduce institutionalized adolescents' aggression, antisocial behavior, anxiety, depression, and negative affect, and increase their cognitive flexibility (in the form of increased impulse control).

## Introduction

### Young People Placed in Juvenile Institutions

The Swedish National Board of Institutional Care (Statens institutionsstyrelse, SiS) runs special residential homes and provides individually tailored compulsory care for young people with psychosocial problems, substance abuse and aggressive antisocial behaviors. Care is provided under the terms of the Care of Young Persons (Special Provisions) Act (LVU) (1990:52) and the Secure Youth Care Act (LSU) (1998:603). The social services of the municipalities are responsible for handling and placing these young people into SiS, as well as taking care of their needs and support after their release from SiS. SiS runs 23 special residential homes in Sweden that currently holds about 700 adolescents in need of special, compulsory care (Personal communication with SiS statistic unit, January 2021).

Every year, the Social services commit over a thousand young people between 15 and 21 years old to SiS's juvenile institutional care due to drug abuse, criminal activity, and/or other socially destructive behaviors. According to SiS (1) the average length of special care in 2019 was 164 days per young person, amounting to ~206,000 care days a year. In 2019, Swedish municipalities alone spent 1.44 billion Swedish crowns (SEK) on young people's care committed to juvenile institutions.

Within this population of children and young adults, the majority has at least one but most often several coexisting psychiatric diagnoses (2), even though the primary reason for the compulsory care is their antisocial behavior, which hampers individual development. The most common diagnosis for both young males and females is Attention-Deficit Hyperactivity Disorder (ADHD), followed by Substance Use Disorder and Post-Traumatic Stress Disorder (PTSD). During the peculiar circumstances of the year 2020, due to the COVID-19 pandemic, a substantial proportion of Swedish adolescents reported more substance use (3) suggesting a possible increased pressure on SiS services in following years.

About half of the young people in the SiS juvenile institutional care report having experienced depression for a longer period of time, attention difficulties, and/or severe anxiety/tension. Almost every other female (47%) and more than 10% (13%) of males has attempted suicide. More than one in three has been the victim of physical and/or psychological abuse by a parental figure. About 40% report having witnessed violence against someone close to them, and nearly half of the females have been victims of sexual abuse (4).

A majority of the young people in SiS care have failed at school, have difficulties keeping up with the teaching, and/or have poor attendance. Their challenges are often complicated, and their environment (family relations, the circle of friends) has often had a substantial impact on their current situation.

The special residential homes run by SiS are the only treatment facilities in Sweden that have the right to forcibly detain individuals who have been taken into compulsory care according to the LVU Act. This right encompasses the options to place individuals under lock and key and/or physically restrain them if they pose a danger to themselves or others. In 2019, physical restraint was used 1,152 times in the residential homes run by SiS (1). According to SiS, most of these events involved a small number of young people and the common factor was a low functioning level, neuropsychiatric disorders, and comorbid psychiatric illness.

Recent research has shown that this population of adolescents has an increased need for improved and integrative treatments. A 3-year follow-up study of institutionalized young people found dramatically increased rates of criminal recidivism, use of inpatient care, and untimely death among young people in institutional care compared to an age-matched general population group (5). The past year's (COVID-19 pandemic) dramatic changes resulted in increased stress, insecurity, fear of illness, risk of an imbalance between school-work and private life, and social isolation. Adolescents reply to these type of traumatic events with an increased incidence of anxiety-, eating disorders, depression, self-harm, suicide, and illegal substance use. A general increase in crime, where violence in close relationships and cyberbullying are some of the most frequent problems, is predicted. These are realities that high schools, social services, health cares, and families have to be prepared to face.

### Psychological/Behavioral Changes Induced by Yoga

In recent decades numerous research studies have investigated the effects and action mechanisms of yoga, often inclusive meditation and specific breathing techniques. Those studies suggest that such activities can have a significant impact on somatic and mental health. It has been shown that yoga increases psychological well-being, self-compassion, and resilience (6–8). For instance, some results suggest that yoga, including meditation and specific breathing techniques, can effectively reduce psychological distress (9, 10), anxiety, and depression (11–13). Yoga combined with controlled, same rhythm breathing was associated with a reduction in suicidal ideation for patients diagnosed with major depressive disorder (14). A specifically developed yoga intervention (trauma-informed yoga) has shown a reduction of symptoms in treatment-resistant PTSD (15).

There are also indications that yoga (including meditation and specific breathing techniques) can have beneficial effects on an individual's neurobiology and increase the capacity to regulate emotions by modulating the activity and connectivity in the prefrontal cortex, anterior cingulate cortex, insular cortex, and the amygdala (16, 17). Yoga improves the sympathetic nervous system's regulation and the hypothalamic-pituitary-adrenal system, which are essential in response to stress (18).

Today it is well-established that the environment (physical, psychological, social, and/or cultural) induces distinct gene expression changes, which can be studied by the emerging field of psychosocial genomics (19) focusing on the relationship between the body, mind, and behaviors. Studies on yoga and other mind-body interventions suggest that these practices positively affect gene expression profiles; for example, they may lead to a reduced risk of inflammation-related diseases (20). Multiple lines of evidence (preclinical, genetics, and bioinformatics) show an activation of immune system molecules and pathways that can contribute to psychiatric disorders' pathogenesis (21–23).

Last year a new review was published of randomized controlled trials testing the effects of yoga with youth (24), which concluded that there is growing evidence that yoga is a promising intervention for children and youth.

### Yoga in Correctional Settings—Our Previous Results

The above-described physiological changes may explain those behavioral and psychological changes observed in our previous study on yoga in the Swedish Prison and Probation Services (9, 25). In recent years, yoga has become popular in many correctional institutions worldwide as a complementary rehabilitation tool offered to inmates. The popularity can be partly explained by its cost and time efficacy compared to other non-pharmacological treatments, such as psychological therapies. Our study shows that regular yoga practice is associated with an increased level of impulse control (25), attenuation of aggression and antisocial behaviors (25), and a significantly decreased level of paranoid ideations (9), each of these phenomena being an essential variable related to criminal behavior. Furthermore, improvements on variables that can increase offenders' abilities to participate in treatments have also been observed, for example, that yoga significantly can increase positive emotional states and decrease emotional states that are negative (25), sustain attention (25), reduce depression, anxiety, and obsession (9), and very importantly, can increase personality traits, that can be interpreted as character maturity (26). Conclusively, our results, as well as other research summarized in a systematic review (27), show that yoga has a strong potential to strengthen the inmates' self-acceptance, purposefulness, and sense of responsibility. These are qualities that promote a more peaceful and safer environment in the correctional settings, providing a foundation for the development of a prosocial lifestyle upon release.

### Role of Yoga for Children and Young Adults at Juvenile Institutions

The overall goal of the treatments offered in SiS's juvenile institutions is to help adolescents adapt to social and cultural norms and become prosocial, healthy citizens. The adolescents' responsivity to such treatments is highly influenced by their sustained attention, compliance, and general mental health. Compulsory care providers experience a great need for new, cost, and time-effective non-pharmaceutical methods that can enhance the responsivity (attention, compliance) of young adults to the methods currently used to change antisocial behavior and treat substance-related syndromes. The most frequently used methods at juvenile institutions are Cognitive Behavioral Therapy, Aggression Replacement Treatment, Relapse Prevention, and Motivational Interview, each of which requires highly educated personal and longer treatment time. Importantly, we do not suggest yoga instead of any well-established treatment methods within SiS, but as a complement where yoga may promote and enhance the effects of ongoing psychological treatments. Yoga may also provide a positive coping tool for adolescents in SiS and potentially offer a prosocial activity upon release from institutions.

There is a lack of research measuring yoga's effects on adolescents' mental health, cognitive psychological characteristics, and deviant behaviors in residential/institutional care. One pilot study examined yoga's effects as a complementary care component in an institutionalized youth population (28). In that study, a multimodality intervention consisting of yoga poses, breathing exercises, and meditation was offered to institutionalized adolescents daily. The results indicate that yoga practice (combined with breathing techniques and relaxation/meditation) may improve stress resilience and self-control in an incarcerated youth population (28). In another pilot study, yoga intervention resulted in decreased alcohol consumption and improved social skills in a population of young people with high-risk behavior (29).

Contemplative preventative practices (manualized meditation-, mindfulness-based intervention) have been suggested in residential psychiatric care for children with severe psychiatric disabilities to reduce their need for physical intervention in response to dangerous behavior (30). A few studies have reported decreased anxiety and/or depression in children and adolescents (not institutionalized) having participated in yoga programs (31–35). It was proven that yoga and mindfulness-based interventions positively affect inattention and hyperactivity in young people with ADHD (36). Notably, a recent review of randomized controlled trials (RCTs) of yoga suggested improvement in behavioral and/or cognitive and/or physiological functioning in children and youth (ages 5–18; not institutionalized) (24).

## Methods

### Participants

Computer required sample size analysis for repeated measures ANOVA within-between interaction, with an effect size of 0.25 [medium effect size; average from effect sizes in changes by yoga in previous studies (9, 25)], a power of 0.80, an alpha error probability at 5%, for two groups (yoga and comparison) and two measurements (pre-and post-intervention) suggested a sample size of 34 for each sex.

We aim to collect complete data from at least 34 participants of both sexes (34 male and 34 female clients) to perform gender-specific analyses. Gender analyses will only be performed, if this number of participants can be reached.

Based on previous experience working with participants within correctional settings, we know that the attrition rate can reach 50%; therefore, our aim is to include approximately 120 participants.

Three institutions at the South West in Sweden have at this stage declared interest in participating in the study. Data collection is planned to take place for one and a half years' time, based on an estimated three months per institute (Figure 1). This three months period includes spreading advertisements and information about the study, collecting informed consents, six weeks of intervention (including pre- and post-intervention tests), and time for qualitative interviews to assess individual experiences of yoga classes. As the average time spent within SiS is calculated to be eight months, we will be able to perform intervention and data collection in each participating institute twice, six months apart during the planned data collection period (one and a half years) (Figure 1).

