### Yoga Classes

The yoga classes held twice a week consist of trauma-informed yoga methods including inviting language, freedom of choice by offering options, a set routine for predictability and recognition, counting down in challenging poses for a sense of control and guidance toward practical interoceptive awareness. The relaxation offered is a progressive muscle relaxation adapted for ADHD and high anxiety levels. The aim is to increase resilience, promote relaxation and to provide self-regulation skills for stress and overwhelming emotions and reactions promoting self-empowerment and impulse control. The class will be set up in a circle to provide a sense of safety with no outer disturbances for triggering responses and will always be offered on a voluntary basis for the participants.

A yoga class is 75 min long and consists of yoga methods such as physical movement, static yoga postures, balance exercises, and breathing practices. The instruction intends to increase the interoceptive awareness with practically adapted mindfulness and guided trauma-informed progressive relaxation. The class includes intervals of raising and lowering heart rate and breathing to provide self-regulating skills. The classes do not consist of potential triggering poses, no physical adjustments or practices that can bear a resemblance to sexual abuse or practices that can over-activate the sympathetic nervous system.

Each class is built up as follows:

Warm-up 15 min: At least 10 min of warm-up exercises to release muscular tension, discharge high-stress levels, restlessness, and anxiety, increase blood circulation, and increase proprioceptive awareness.Opening sequence 15 min: large energizing dynamic movements.Balancing poses 10 min.Dynamic Sequence 15 min: a combination between dynamic energizing movements and powerful postures where the participants hold the pose for at least two min (impulse-control). The importance of synchronized breathing and movements.Closing 20 min: including the last 10 min with guided mindfulness-based relaxation.

The instructors have completed a special training program in trauma-informed yoga and yoga for mental health, and they are trained in how to manage overwhelming emotions in a class. The classes are adapted to the most common mental health issues presented within the juvenile institutional system, such as PTSD, anxiety disorders, depression, ADHD, and autism.

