### Data Analysis

If the required number of male and female participants (at least 34 of each gender) is reached, then we will analyze the data separately by gender. Otherwise, the data will be pooled, and no gender-specific results will be presented.

All statistical analyses will be conducted using a significance level of *p* <0.05. Only complete post-attrition data will be analyzed. The comparison of the attrition rates between the two groups (“yoga” group and “comparison” group) will be calculated using Fisher's exact test. The Test 1 and 2 scores within the groups will be compared using the Wilcoxon signed-rank test. Mean changes and standard deviations will be calculated to identify differences within the groups. Mann–Whitney *U-*tests will be used for the continuous variables and Fisher's exact test for the categorical variables to compare differences between them. The effect sizes (Cohen's *d*) will be calculated to identify differences between the groups; an effect size of 0.2 will be considered a small effect, 0.5 a medium effect, and 0.8 a large effect. As data will be collected from three institutions, generalized estimating equations (GEE), that adjusts standard regression estimators for clustering, will be applied. The primary outcome is the level of psychological distress (BSI). Secondary outcomes' (craving, pain, affect, and aggressive antisocial behaviors) mediating and moderating effect will be also explored by conditional process analyses. We plan to conduct a mid-point analysis (about nine months after that data collection has started) to allow for better modeling of change trajectories.

To describe the adolescents' experiences of participating in yoga practice, with the help of a semi-structured interview guide (Supplementary Material), individual interviews will be performed. The adolescents will be contacted within 2 weeks after completing the yoga intervention. Content analysis will be used as a method for analyzing the interviews (52). The qualitative content analysis is performed stepwise identifying meaning units, condensing the meaning units, labeling meaning units with codes and thereafter identifying subcategories, categories ant themes. Content analysis makes it possible to describe the adolescents' experiences on both manifest and latent levels.

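### The 80% power for 34 per sex is calculated for an ANOVA on independent adolescents that is not in the analysis plan; it is not demonstrated for the planned rank and cluster-adjusted tests, which also may not hold 5%

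*Protocol article*

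**What the plan says.** The Participants section of the protocol article gives the basis of its sample size as follows: "Computer required sample size analysis for repeated measures ANOVA within-between interaction, with an effect size of 0.25". Power is set at 0.80 and alpha at 5%, and the calculation "for two groups (yoga and comparison) and two measurements (pre-and post-intervention) suggested a sample size of 34 for each sex". No pre-post correlation, intraclass correlation (ICC) or design effect is listed. Sex-specific analyses are done only if 34 of each sex complete; otherwise the sexes are pooled. About 120 are to be recruited against attrition of up to 50%, at three institutions that each run the intervention twice.

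The Data Analysis section plans Wilcoxon signed-rank tests within groups. Between groups, Mann-Whitney U tests "will be used for the continuous variables". It then adds: "As data will be collected from three institutions, generalized estimating equations (GEE), that adjusts standard regression estimators for clustering, will be applied". BSI, the measure of psychological distress, is named as primary outcome. The section does not say which between-group method decides the primary comparison.

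The Yoga Classes section shows that the intervention is delivered to a group: "The class will be set up in a circle to provide a sense of safety". The Procedure section lets participants choose their group, and comparison participants take whatever leisure-time activity the institution offers.

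**The concern.** The power statement and the analysis belong to different models. The sizing treats every adolescent as independent and tests a group-by-time interaction by ANOVA. The analysis uses a rank test, then a regression method chosen because the observations are held to be clustered. A plan that acknowledges clustering in its analysis and allows nothing for it in its sizing has not shown that 34 per sex gives 80% power.

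The correlation that matters for power is not mainly the institution. Both groups are present in each institution, so an institution effect largely cancels in the comparison. The candidate is the yoga class: adolescents who share sessions and an instructor may change together.

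Two things are at stake: whether the per-sex 80% can be quoted for the planned tests, and whether those tests reject at 5% when yoga has no effect.

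**Working it through.** **Inputs from the article.** Effect size 0.25 (read as Cohen's f), power 0.80, alpha 5%, two groups, two measurements, N = 34 per sex, three institutions × two rounds = six cycles.

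**Assumptions, not in the article.** Pre-post correlation r = 0.5; equal groups (17 v 17); one yoga class per cycle, so 17/6 ≈ 3 yoga completers of one sex per class; class ICC 0 to 0.10; normal change scores; class correlation in the yoga group only.

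**1. The plan's own figure.** For the within-between interaction, λ = f²·N·m/(1 − r), with 1 and N − 2 degrees of freedom.
- N = 34: λ = 0.0625 × 34 × 2 / 0.5 = 8.5, power 0.807.
- N = 32: power 0.781.

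So 34 is the smallest even N that reaches 80%. It reproduces, with 0.7 points to spare. It is the same as a two-sample t test on change scores with a standardised difference of 1.0, since 1.0² × 17/2 = 8.5.

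**2. The planned rank test, independent data.** Simulated Mann-Whitney power at 17 v 17 and a difference of 1.0 is about 0.78. It takes 18 v 18 (N = 36) to return to 0.807.

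**3. Adding class correlation, 17 v 17, six yoga classes.**

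| Method | ICC 0 | ICC 0.05 | ICC 0.10 |
|---|---|---|---|
| Mann-Whitney, classes ignored | 0.78 | 0.78 | 0.77-0.78 |
| Class-mean Welch test (six yoga class means against 17 individuals) | 0.77 | 0.74 | 0.72 |

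The first row changes little because the test ignores the correlation; the cost appears in its type I error (step 5). The second row respects the classes, but is only an illustration. Part of its loss is present at ICC 0 and is the price of reducing 17 adolescents to six means. A design-effect approximation, 1 + (m − 1)·ICC in the yoga group only, with m = 3, gives 0.79 at ICC 0.05 and 0.77 at 0.10.

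**4. Institution correlation and pooling.** With an institution ICC of 0.05-0.10 shared by both groups and no class effect, Mann-Whitney power at 17 v 17 is 0.79-0.81, so nothing is lost. With the sexes pooled, the ANOVA formula gives 0.98 at N = 68 and 0.97 at N = 60. Mann-Whitney at 30 v 30 with six classes stays at about 0.94 even at class ICC 0.20.

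**5. Rejection when yoga has no effect.**
- Mann-Whitney, 30 v 30, six classes ignored: 6.1% at ICC 0.05 and 6.8% at ICC 0.10. At 17 v 17 the excess is smaller, with rejection no higher than about 6%.
- GEE with three institutions as clusters, exchangeable correlation, uncorrected sandwich errors, 17 v 17, institution ICC 0.05: 25.4% of 800 runs.
- Class-mean Welch test, six classes: 5.0-5.3%.

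**The case against.** **The 34 is not wrong, and the named test loses little.** Both stand. A reader might infer that 34 was miscalculated; it was not. A reader might also infer that the trial is shown to miss its power. The documents do not support that: the rank test alone costs 2 to 3 points, the article gives no ICC or class size, and the pooled fallback is well above 80% at the assumed effect. What can be said is that the per-sex 80% is not demonstrated.

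**The lower figures belong to a test nobody plans.** This stands too. The 72-77% comes from a class-mean test found neither in the article nor in the fix below. It shows the direction and rough size of the loss, and should not be printed as the trial's power.

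**Clustering in the yoga group only is an assumption.** Correct. Comparison activities include a physical education class, which is also group delivery, so comparison participants may be clustered as well. On the other side, the standardised yoga manual and common instructor training may keep the class ICC low.

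**The GEE already covers this.** In principle it does: classes are nested in institutions, so institution-level robust errors absorb class correlation, and a group-by-time GEE targets the same contrast as the ANOVA. In practice three clusters are too few for uncorrected robust errors, as the 25% shows. The article names no correction. One may be specified in a document not shown, in which case that figure does not apply.

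**These details belong in an analysis plan.** An ICC or a working correlation often does. But the article itself fixes both the sizing model and the tests, and they do not match.

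**Conclusion.** The point holds as a mismatch between sizing and analysis. The 80% per sex is the power of an ANOVA on independent data. For the planned Mann-Whitney test it is about 78% with independent data; for a test that respects yoga classes it is lower by an amount that cannot be fixed from the article. All these figures rest on the plan's own effect size, a pre-post correlation of 0.5 and equal groups.

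The power gap concerns only the sex-specific analyses. The error-rate problem can also affect the pooled analysis: about 6-7% for Mann-Whitney with six classes at ICC 0.05-0.10. It is far larger for a three-cluster GEE if its errors are left uncorrected (about 25%, simulated at 17 v 17). A rejection rate of that size could change the primary conclusion, which is why this deserves a change to the analysis and not only to the wording.

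**What to change.** 1. **Participants.** Keep 34 per sex. State its power for the primary between-group model that will be used, computed for that model over a stated ICC range and class size, with the assumed pre-post correlation. Say that it may be below 80%.
2. **Data Analysis.** For the primary outcome (BSI), replace the Mann-Whitney test and the three-cluster GEE with one model. It should have institution as a fixed factor, a random effect for yoga class (institution × round), comparison participants as singletons unless they also share a group activity, and small-sample degrees of freedom.

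No extra participants are needed. The costs are a slightly less favourable stated power and a slightly wider interval. With so few classes, the class variance will also often be estimated as zero: in simulations with 17 yoga completers in six classes, a moment estimate was zero or negative in 47% of runs at ICC 0.05 and 40% at ICC 0.10. The plan should say in advance what is done in that case.

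### The 34 per sex is sized for a difference in change of about 1.0 SD, which the plan labels a medium effect although its own between-group scale puts large at 0.8

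*Protocol article*

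**What the plan says.** The Participants section names its method as "Computer required sample size analysis for repeated measures ANOVA within-between interaction". The assumed effect is given in these words: "with an effect size of 0.25 [medium effect size; average from effect sizes in changes by yoga in previous studies". Power is set at 80% and alpha at 5%, and the result is reported as follows: "for two groups (yoga and comparison) and two measurements (pre-and post-intervention) suggested a sample size of 34 for each sex". The section does not say whether 0.25 is Cohen's f or another measure, and it gives no pre-post correlation and no allocation ratio.

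The Data Analysis section uses a different scale. Differences between the groups are to be expressed as Cohen's d, where "an effect size of 0.2 will be considered a small effect, 0.5 a medium effect, and 0.8 a large effect".

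The 34 also works as a decision rule. Under Data Analysis, sex-specific analyses are run only when both sexes reach that number, and the sexes are combined when they do not. The Participants section expects attrition of up to 50% and aims to enrol about 120.

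**The concern.** The two sections use the word "medium" for different things, and the document never converts one to the other. Taking both at face value, one would conclude that 34 completers of one sex give 80% power for a medium difference between yoga and comparison as the plan defines medium. If the 0.25 stands for something much larger on the d scale, that conclusion is wrong.

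This matters because 34 decides whether the data are split by sex, and because the power statement governs how a non-significant result will be read. A null result means little if the analysis had limited power for the effect size that the plan itself calls medium.

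**Working it through.** **Inputs.** From Participants: effect size 0.25, power 0.80, alpha 0.05, two groups, two measurements (m = 2), N = 34 per sex, attrition up to 50%, about 120 enrolled. From Data Analysis: d = 0.2, 0.5 and 0.8 as small, medium and large. Assumed, because not stated: 0.25 is Cohen's f, the pre-post correlation is ρ, and the groups are equal.

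**1. Reproducing 34.** For the within-between interaction, λ = f² × N × m / (1 − ρ), with 1 and N − 2 degrees of freedom. With f = 0.25, N = 34 and ρ = 0.5:

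λ = 0.0625 × 34 × 2 / 0.5 = 8.5, with 1 and 32 degrees of freedom, power 0.807.

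This is the smallest even N that reaches 0.80. Other correlations give other totals:

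| ρ | 0 | 0.3 | 0.4 | 0.5 | 0.6 | 0.7 | 0.8 |
|---|---|---|---|---|---|---|---|
| N | 66 | 46 | 40 | **34** | 28 | 22 | 16 |

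Two other effect-size conventions for the same design give 128 and 130. Of the variants tried, only f = 0.25 with ρ = 0.5 returns 34.

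**2. What f = 0.25 means between groups.** In a 2 × 2 interaction the four cell deviations are ±Δ/4, where Δ is the between-group difference in change. So f = Δ/(4σ), and Δ = 4 × 0.25σ = 1.0σ. The SD of change is σ√(2(1 − ρ)), which equals σ at ρ = 0.5, so d = 1.0 on either standardiser. As a check, a two-sample t-test on change scores with 17 per group and d = 1.0 also gives power 0.807.

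**3. Power of 34 completers on the plan's own d scale** (17 per group, ρ = 0.5):

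| d | power |
|---|---|
| 1.0 | 81% |
| 0.8 (large) | 62% |
| 0.5 (medium) | 29% |

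The smallest difference detectable with 80% power is 0.99 SD. For d = 0.5, 80% power needs 64 per group, or 128 completers.

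**4. Which analysis is likely.** 120 × (1 − 0.50) = 60 completers. The split needs 34 + 34 = 68. At the plan's own attrition figure the split is therefore not triggered and the data are pooled.

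**5. Sensitivity to the unstated correlation.** Power for a difference in change of 0.5 raw SD, with equal groups; the noncentrality uses 0.5/√(2(1 − ρ)):

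| completers | ρ = 0.3 | ρ = 0.5 | ρ = 0.7 | ρ = 0.8 |
|---|---|---|---|---|
| 34 (one sex) | 22% | 29% | 45% | 61% |
| 60 (pooled) | 36% | 48% | 69% | 85% |
| 68 (pooled) | 40% | 53% | 75% | 90% |

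If d is standardised by the SD of change, the ρ = 0.5 column applies at every correlation. At ρ = 0.5 the pooled sample detects 0.74 SD (60 completers) or 0.69 SD (68 completers) with 80% power.

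**The case against.** The strongest reply is that nothing was miscalculated. The 34 is correct for its input, 0.25 is the conventional medium value for Cohen's f, and the d scale in Data Analysis is for reporting results. The protocol never says that it is powered for d = 0.5. This stands in part: a reader might infer an arithmetic error, and there is none. But the plan prints no metric for 0.25, and the only effect-size scale it defines is d. On that scale the word "medium" is wrong for the difference being powered.

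A second reply is that the 29% belongs to an analysis that may never be run. That is right. A reader might infer that the whole study has 29% power for a medium effect. The documents do not support this, because with 60 expected completers the pooled analysis applies, with about 48% at correlation 0.5.

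A third reply is that the correlation is inferred. That is also right. With d in raw-SD units and a correlation of 0.8, the pooled analysis passes 80% power, so one cannot say that the study is underpowered for d = 0.5 under every assumption. The single-sex analysis stays below 80% across 0.3 to 0.8.

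Fourth, 0.25 is described as an average from earlier yoga studies. Those are not available here, so whether a 1.0 SD difference is realistic cannot be judged.

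Two further arguments are tempting and are left out. Participants choose their group, so a 17/17 split is not assured, but the documents give no expected split and any figure would be only illustrative. The planned tests include Mann-Whitney and GEE rather than the ANOVA used for sizing, but no loss of power from this has been quantified.

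**Conclusion.** The point holds as an effect-size labelling error. The calculation behind 34 per sex targets a between-group difference in change of about 1.0 SD, above the plan's own threshold for a large effect. For the plan's medium effect, a single-sex analysis of 34 has about 29% power: 22% to 61% for correlations 0.3 to 0.8 with d in raw-SD units, or 29% at any correlation if d uses the SD of change. The more likely pooled analysis has about 48% with 60 completers and 53% with 68 at correlation 0.5 (36% to 85% and 40% to 90% over the same range).

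These figures assume equal groups, a two-sided 5% test on change scores, and independence between participants. The correlation of 0.5 is inferred from the fact that it reproduces 34.

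**What to change.** In the Participants section:

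- State that 0.25 is Cohen's f for the group-by-time interaction, and state the pre-post correlation (0.5, if that was the value used) and the equal-group assumption.
- Delete "medium", or replace it with the d equivalent: 34 completers give about 80% power for a difference in change of about 1.0 SD.
- Add that, at correlation 0.5, the pooled 60 to 68 completers detect about 0.7 SD with 80% power.
- Do not present 34 per sex as adequate for a medium effect.

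The cost is rewording one paragraph. No participants are added and no analysis changes; the stated power becomes less favourable.
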